### Withdrawal or dropout criteria

In this study, the intervention measures for both the trial group and the control group may be stopped if the subject meets any of the following criteria: (1) the subject requests to withdraw from the clinical study; (2) the subject is unable to complete the relevant test as needed, which affects the data collection; (3) the subject receives other treatments during the treatment period without authorization; (4) the subject experiences adverse events or serious adverse events during the trial that require their withdrawal from the study; (5) the subject experiences significant worsening of the disease, complications or special physiological changes that require their withdrawal from the study; (6) the researcher considers it unsuitable for the subject to continue participating in this study.

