### Outcomes

Prior to the intervention, individuals who expressed interest in participating in the study were invited to schedule an appointment for additional information.

If they choose to participate, they will sign an informed consent form and be screened by independent researchers to determine if they meet the inclusion and exclusion criteria. Participants who meet all the inclusion criteria and none of the exclusion criteria will be included in the study. Descriptive data, including general information such as age, sex, race, occupation, height, weight, body mass index (BMI), blood pressure, education level, medical history, medication use, smoking status, drug use, and alcohol consumption, will be carefully collected before randomization. In addition, all participants were assessed using three scales: the JOA, the VAS, and the NDI.

Both the intervention group and the control group completed a total of 12 rehabilitation sessions over a period of 4 weeks. Outcomes will be assessed immediately after the 4-week intervention period and compared with baseline data. The primary outcome will be the change in functional ability, assessed using a standardized functional assessment tool (JOA score). The secondary outcome measures will include pain level (VAS score), neck disability (NDI score), and changes in the functional areas of the brain.

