### Safety assessment

Any adverse events such as discomfort caused by MRI procedures, headache, or VR training that cannot be tolerated will be recorded throughout the intervention period and reported to the ethics committee to ensure safety. Operators conducting GRAIL procedures should be familiar with the trial protocol and procedures related to safety, and ethics must strictly follow the Grail operation guidelines. In case of an adverse event during the intervention, the participant will receive appropriate medical care, and all the details will be recorded and reported to the principal investigator and ethics committee to determine if the participate should continue the trial. All collected adverse events will be truthfully reported in future publications, and the incidence rate of adverse events will also be considered in the analysis.

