### Sample size calculation

The goal of our study was to investigate the effectiveness of VR technology in the rehabilitation of patients with CSM after surgery. Due to a lack of research on the effect of VR technology on the rehabilitation of CSM patients after surgery, we conducted a small-sample pilot study. The sample size was estimated based on the improvement in JOA scores for cervical spondylosis reported by the Japanese Orthopaedic Association. One month after surgery, the average JOA scores and SDs for the VR rehabilitation intervention group (*n* = 10) and the conventional rehabilitation group (*n* = 10) were 15.30 (SD = 0.90) and 14.7 (SD = 0.78), respectively, with an effect size (Cohen’s *D*) of 0.71. Using the Gpower 3.1 software, we calculated the needed sample size, which, with a type I error of *α* = 0.05 and a type II error of *β* = 0.2, was estimated to be a sample size of *n* = 64. Considering a dropout rate of 20%, 39 participants were needed for each group, for a total of 78 participants. Finally, we randomly allocated the 78 participants into a VR training combined with rehabilitation intervention group and a conventional rehabilitation group, each consisting of 39 participants.

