### Statistical analysis

All nonimaging data will be analysed using SPSS version 21 by an independent statistician who is blinded to the treatment and control groups to ensure objectivity and reduce bias. The statistical significance level for testing will be set at 0.05 with a two-tailed test. Continuous variables are presented as the mean, standard deviation, or maximum or minimum values based on their statistical distributions. Independent sample *t* tests or nonparametric tests (Mann–Whitney *U* test) will be used to compare the results presented as continuous variables and mean values to validate the effectiveness of the intervention. Furthermore, intra- and intergroup comparisons were made at 4 weeks to observe the differences between the two intervention methods. If necessary, logistic regression, general linear correlation, or regression was used to compare different types of results based on the variable type and distribution. Basic data comparisons between the treatment and control groups will be performed using *t* tests, chi-square tests, or nonparametric tests. Participants who drop out during the intervention period will not be excluded according to the intention-to-treat principle, and missing data will be replaced using the last observation carried forward method to maintain statistical power and avoid bias.

The amplitude of low-frequency fluctuation (ALFF) is an indicator of the amplitude energy of the low-frequency spectrum and reflects the spontaneous activity of neurons in the resting state of the brain. The ALFF is a useful tool for analysing functional MRI data to study longitudinal neural changes and explore the relationship between brain plasticity and the recovery of sensory and motor function induced by stimulation [22]. In this study, the REST 1.9 software from Beijing Normal University (http://www.restfmri.net/) was used to perform linear drift and calculate the amplitude of signal oscillation in each voxel in the low-frequency range (0.01–0.1 Hz) to obtain ALFF images. Finally, the ALFF values of each participant were *Z*-transformed for further statistical analysis.

Longitudinal measurements in a resting-state task and further correlation analysis of imaging and scale score data obtained from baseline and postintervention measurements were performed to explore the relationships between brain remodelling and postoperative sensory and motor function recovery in CSM patients.

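### Last observation carried forward neither maintains power nor avoids bias here: it enters anyone who drops out before week 4 with a JOA change of exactly zero

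*Protocol article*

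**What the plan says.** The Statistical analysis section keeps participants who drop out during the intervention in the analysis under intention to treat, and adds that "missing data will be replaced using the last observation carried forward method to maintain statistical power and avoid bias". The tests named are the independent-samples t test or the Mann–Whitney U test, and "The statistical significance level for testing will be set at 0.05 with a two-tailed test".

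The primary outcome is change in JOA. On timing, the Outcomes section says: "Outcomes will be assessed immediately after the 4-week intervention period and compared with baseline data". The Neuroimaging scans section agrees that all scales are taken before the intervention and repeated after 4 weeks. The Primary outcome measurement section also mentions JOA at follow-up, without a date.

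The Sample size calculation section allows for losses: "Considering a dropout rate of 20%, 39 participants were needed for each group, for a total of 78 participants".

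**The concern.** Carrying the last observation forward needs an observation after baseline to carry. Here a participant lost during the 4 weeks has only the baseline JOA, so the rule becomes baseline carried forward and the imputed change is zero. Participants enter between 24 hours and 3 months after decompression, and both arms receive rehabilitation, so zero is a poor guess for most of them. If the pilot used the trial's entry range, its VR mean of 15.30 lies above the entry ceiling of 15, so average change in that arm was above zero. The rule can also err the other way, because marked worsening is a listed withdrawal reason and would be scored as no change.

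Two things are at stake. First, the 20% allowance inflates the sample as if dropouts contribute nothing, whereas the analysis enters them as zeros, which pulls the arms together and widens the spread. Second, if more people are lost from one arm than the other, that arm receives more zeros and a difference arises with no treatment effect behind it. The article gives reasons to think this possible. Adverse events to be recorded include "VR training that cannot be tolerated", which only the VR arm can experience. Another withdrawal reason is that "the subject receives other treatments during the treatment period without authorization", which may be commoner in control participants who know their allocation.

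**Working it through.** **Inputs from the Sample size calculation section.** Pilot JOA means in the VR and control groups "were 15.30 (SD = 0.90) and 14.7 (SD = 0.78), respectively"; the calculation was made "with a type I error of *α* = 0.05 and a type II error of *β* = 0.2"; 64 evaluable, 20% dropout, 39 per arm.

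**The plan's own figure.** Pooled SD = √((0.90² + 0.78²)/2) = 0.842; d = 0.6/0.842 = 0.712, stated as 0.71. By the normal approximation, n per arm = 2 × ((1.960 + 0.842)/0.71)² = 31.1, rounded up to 32, so 64 in total. This reproduces. 32 × 1.2 = 38.4, rounded up to 39 per arm, gives 78. With 20% lost, 39 × 0.8 = 31.2 per arm remain, and two-sided t-test power in completers is about 79%.

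**Effect of the rule with equal dropout.** Let m be mean control recovery, m + 0.6 mean VR recovery, s the SD of change, and 20% of each arm set to zero.
- Expected difference = 0.8(m + 0.6) − 0.8m = 0.48, whatever m is.
- Variance in an arm = 0.8s² + 0.16 × (mean recovery in that arm)².

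Example with m = 1.7 and s = 0.842: VR variance = 0.567 + 0.16 × 2.3² = 1.414; control variance = 0.567 + 0.16 × 1.7² = 1.030; pooled SD = √1.222 = 1.105; d = 0.48/1.105 = 0.434; power with 39 per arm is 47%.

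The article does not give m or s. I assume a range for m (the entry range of 5 to 15 allows a wide one) and use the pilot post-score SD for s:

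| Assumed control recovery m (points) | Pooled SD | t-test power |
|---|---|---|
| 0 | 0.772 | 77% |
| 0.35 | 0.806 | 74% |
| 0.7 | 0.861 | 68% |
| 1.7 | 1.105 | 47% |
| 2.7 | 1.422 | 31% |
| 4.7 | 2.141 | 17% |

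The Mann–Whitney test, simulated on half-point scores, gives about 46–62% for m from 0.7 to 4.7, against about 76% in completers. If s is 1.5 instead, completer power is 34%, and the rule gives 34% at m = 0, 32% at m = 0.7 and 14% at m = 4.7.

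**Type I error with equal dropout.** With no true effect and 20% lost from each arm, simulated t-test type I error is about 5% at m = 0.7, 2, 2.7 and 4.7.

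**Unequal dropout (hypothetical).** With no true effect, the expected VR minus control difference = −(VR dropout − control dropout) × m. At m = 2 and s = 0.842:
- 15% control, 25% VR: −0.10 × 2 = −0.20 points; simulated type I error about 12%.
- 10% control, 30% VR: −0.20 × 2 = −0.40 points; simulated type I error about 36%.

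With a true effect of 0.6, the second pattern leaves 0.7 × 2.6 − 0.9 × 2 = 0.02 points. The opposite imbalance gives 0.9 × 2.6 − 0.7 × 2 = 0.94.

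**The case against.** A reader might infer that the rule is known to cut power to somewhere between 17% and 69%. The documents do not support that. The range needs a mean recovery of 0.7 to 4.7 points, a post-score SD standing in for the SD of change, equal dropout and a t test. The pilot means were taken one month after surgery, while trial participants reach week 4 roughly one to four months after surgery, so recovery in late enrolees may be small; at zero recovery the loss is only from 79% to 77%. With a larger SD of change, most of the shortfall comes from that SD. A spike of zeros well away from the other values is also where the Mann–Whitney option would be expected, and it does not fall to 17%. All of this stands.

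A reader might also infer that the rule inflates false positives in this trial as planned. It does not if dropout is equal, and the article gives one 20% allowance with no split by arm. The withdrawal section lists reasons for stopping the intervention; it does not say that such participants miss the week-4 assessment. The undated follow-up JOA means that one post-baseline visit is not the whole schedule, but a later score cannot be carried back to week 4.

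The trial calls itself exploratory, and sensitivity analyses may be in an analysis plan not shown. That does not rescue a primary rule which the article fixes and justifies on two grounds that both fail.

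**Conclusion.** The concern holds for the stated justification and the choice of rule. For anyone lost before week 4 the imputed JOA change is zero by construction. At 20% dropout per arm the expected difference falls by a fifth, from 0.60 to 0.48, without any assumption about recovery. In every scenario tried, power was no better than in completers. The size of the loss depends on recovery and on the SD of change, neither of which is reported: it ranges from negligible near zero recovery to most of the power at 4.7 points. Bias is the graver risk but is conditional: it needs dropout that differs by arm, and equals the dropout gap times mean recovery when there is no true effect. VAS and NDI are on the same baseline and week-4 schedule and are affected in the same way.

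**What to change.** In the Statistical analysis section, delete the closing clause that claims power and freedom from bias, and drop last observation carried forward as the primary rule. Analyse participants in their randomised arms, with week-4 JOA modelled on arm and baseline JOA. Use every observed week-4 value, including those of participants who stopped treatment but were assessed, or use multiple imputation under missing at random. Without imputation, this is in effect a baseline-adjusted analysis of those assessed at week 4, and the text should say so. Keep zero change only as one scenario in a sensitivity analysis that shifts the imputed values separately by arm. State in the Sample size calculation section that the 20% allowance assumes this analysis.

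The cost is a sentence or two of text and a short script, with no extra participants. Recruitment was still open at submission, so the change could be made before analysis. The downside is reliance on missing at random, which the arm-specific sensitivity analysis probes.

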**Methods:**

The purpose of this randomized controlled trial was to evaluate the efficacy of combining VR technology with conventional rehabilitation strategies for the postoperative rehabilitation of patients with CSM. A total of 78 patients will be recruited and randomized to either the conventional rehabilitation group or the group subjected to VR technology combined with conventional rehabilitation strategies. The Japanese Orthopaedic Association (JOA) scale will be the main tool used, and secondary outcomes will be measured via the visual analogue scale (VAS), neck disability index (NDI), and functional MRI (fMRI). The data analysis will identify differences between the intervention and control groups as well as any relationship between the intragroup changes in the functional area of the brain and the subjective scale scores after the intervention.

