The central nervous system (CNS) has been confirmed to be able to reorganize structurally and functionally after injury, enabling repair through neuroplasticity [7]. Brain plasticity is the brain’s ability to modify its structure and function to adapt to environmental changes and experiences [8]. Researchers revealed that the recovery of neural function in CSM patients depends on both spinal cord compression and injury as well as brain function reorganization or plasticity [9]. Moreover, cortical plasticity compensates for some function by involving brain regions that are not primarily involved in a specific task [10]. Therefore, when spinal cord injury occurs, cortical plasticity also occurs. Sabbah, P. et al. discovered that cortical reorganization, either physically or via mental imagery, could activate the lower limb cortical network years after injury and is therefore an adaptive remodelling response known as cortical-spinal neural plasticity [11]. Liu, M. et al. conducted a study using volumetric magnetic resonance imaging (MRI) with voxel-based morphometry (VBM) on 41 CSM patients both before and after surgery and compared the VBM measurements to those of a control group [12]. They assessed the changes in the cortical grey matter volumes in CSM patients before and after surgery and found that, compared to those in the control group, the grey matter volumes in the left caudate nucleus and the right thalamus were lower in the preoperative CSM patients. Six months after surgery, the bilateral grey matter volume in the posterior cerebellar lobes decreased in the postoperative CSM patients, while the grey matter volume in the brainstem was greater than that in the preoperative CSM patients. Compared to the control group, the postoperative CSM patients in the present study had a significantly lower grey matter volume in the left caudate nucleus but higher grey matter volumes in the right inferior temporal gyrus, right orbitofrontal cortex (OFC), and bilateral lingual gyri/cuneus/precuneus cortex. Therefore, based on the scientific theory of brain plasticity, it is important to select appropriate methods to regulate the CNS and promote spinal cord recovery after surgery to ensure the smooth rehabilitation of CSM patients. In recent years, VR technology has been increasingly applied in clinical treatment, particularly for incomplete spinal cord injury, stroke, Parkinson’s disease, and other areas, to promote rehabilitation through brain remodelling [13–15]. This technology could also be a potential therapeutic option for CSM patients after surgery.

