### Study aim

The main objective of this randomized controlled trial was to evaluate the effectiveness of virtual reality technology in the postoperative rehabilitation of patients with CSM. The secondary objective was to explore the potential patterns of cortical plasticity related to sensory and motor function recovery in CSM patients via pre- and postintervention fMRI and longitudinal JOA studies to provide a theoretical basis for investigating the central role of virtual reality training in promoting brain plasticity in patients who have undergone surgery for cervical spondylosis.

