## Enrolment

### Inclusion criteria

All participants who met the following criteria were included: (1) diagnosed with CSM and underwent surgery between 24 h and 3 months prior to enrolment; (2) aged between 20 and 75 years of either sex; (3) a Japanese Orthopaedic Association (JOA) score of 5 to 15; (4) no less than a primary school education; (5) no cognitive dysfunction; and (6) understood the study, agreed to participate in the study, and signed the informed consent form.

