#### Neuroimaging scans

The data for this study were collected at the Radiology Department of Yueyang Hospital of Integrated Traditional Chinese and Western Medicine, which is affiliated with the Shanghai University of Traditional Chinese Medicine. Participants were positioned in the supine position, and their heads were secured using a specially designed head mask. All magnetic resonance imaging (MRI) scans were performed using a Siemens Magnetom Verio 3. T MRI scanner. Resting-state functional MRI (fMRI) data were obtained using a single-shot echo-planar imaging (EPI) sequence with interleaved scanning of 43 slices, a flip angle of 90°, a matrix of 64 × 64, a TR of 300 ms, a slice thickness of 3.0 mm, an FOV of 230 × 230 mm^2^, and a gap of (voxel size of 3.6 × 3.6 × 3.0 mm^3^). T1-weighted structural scans were obtained using a weighted fast spoiled gradient-echo (FSPGR) sequence with TR/TI/TE of 190/900/2.93 ms, a flip angle of 9°, an FOV of 256 × 256 mm^2^, a slice thickness of 1.0 mm, a matrix of 256 × 256, and an average of 1.0. All assessments involving scales and MRI scans were conducted prior to the intervention and then repeated after 4 weeks of intervention.

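### The exploratory correlation of brain change with scale scores ignores time since surgery, which ranges from one day to three months at entry, so part of any correlation may reflect a shared post-operative course

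*Protocol article*

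**What the plan says.** The Study aim section sets a secondary objective to "explore the potential patterns of cortical plasticity related to sensory and motor function recovery in CSM patients". Three other parts of the protocol article determine how it is answered.

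- **Analysis.** The last paragraph of Statistical analysis names a "further correlation analysis of imaging and scale score data obtained from baseline and postintervention measurements were performed to explore the relationships". The abstract (Methods) describes the target as "any relationship between the intragroup changes in the functional area of the brain and the subjective scale scores after the intervention". No covariate is named. Regression appears only as an option to be used where needed, again without covariates.
- **Timing of measurements.** Under Neuroimaging scans: "All assessments involving scales and MRI scans were conducted prior to the intervention and then repeated after 4 weeks of intervention". Each patient therefore contributes one four-week change in ALFF and one in each scale.
- **Who enters.** Inclusion criterion 1 admits a patient "diagnosed with CSM and underwent surgery between 24 h and 3 months prior to enrolment".

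Time since surgery is not in the list of baseline data (Outcomes), is not a stratification factor (Randomization and allocation concealment), and is not mentioned in Statistical analysis.

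The Background reports that the brain changes after decompression without VR: "Six months after surgery, the bilateral grey matter volume in the posterior cerebellar lobes decreased in the postoperative CSM patients".

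**The concern.** A four-week change that starts the day after decompression covers a different part of the post-operative course from one that starts three months later. If post-operative stage affects both the JOA change and the ALFF change, patients at the same stage will tend to be high or low on both. A correlation that ignores stage then shows an association even when ALFF and function have no direct connection. Computing it separately by arm does not help, because each arm contains the whole enrolment window.

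At stake is the reading of the secondary objective. The Statistical analysis section introduces ALFF as a way to "explore the relationship between brain plasticity and the recovery of sensory and motor function induced by stimulation". An association produced by surgical timing would not bear on that question.

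**Working it through.** **The plan's own figures.** The document gives no figure for the correlation analysis. The sample size supplies only the values of n. From the pilot, d = 0.6 / sqrt((0.90² + 0.78²)/2) = 0.6 / 0.842 = 0.71. A two-sided t test at 0.05 with 80% power needs 32 per arm, 64 in total, which reproduces the stated 64. The planned enrolment is 39 per arm, 78 in total.

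**Spread of post-operative stage.** Entry is at about day 1 to day 90. Adding 28 days, the second assessment falls at about day 29 to day 118.

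**Smallest significant |r|** (two-sided 0.05), from r = t / sqrt(n − 2 + t²): 0.316 for n = 39, 0.246 for n = 64, 0.223 for n = 78.

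**Induced correlation.** Let the same function of time since surgery explain a share a of the variance of JOA change and a share b of the variance of ALFF change, with no other link. Then the expected r is sqrt(a × b). The documents give neither share, so equal shares of 10%, 20% and 30% are assumed, giving r = 0.10, 0.20 and 0.30. Unequal shares give less than the larger one suggests: a = 0.30 with b = 0.05 gives sqrt(0.015) = 0.12. If either share is zero, r is zero.

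**False-positive rate of the unadjusted correlation.** Simulation with 4,000 runs per cell, time since surgery uniform over 1 to 90 days, exponential recovery with a time constant of 45 days:

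| Assumed share in each measure | Expected r | n = 39 (one arm) | n = 64 (pooled) | n = 78 (pooled) |
|---|---|---|---|---|
| 0% | 0 | 5% | 5% | 5% |
| 10% | 0.10 | 9% | 11% | 14% |
| 20% | 0.20 | 22% | 37% | 42% |
| 30% | 0.30 | 47% | 69% | 78% |

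**Check by hand.** With the Fisher transformation, the rate is approximately Φ(m − 1.96) + Φ(−m − 1.96), where m = atanh(r) × sqrt(n − 3). For r = 0.30 and n = 39, m = 0.3095 × 6 = 1.857, and the rate is about 46%, in line with the simulated 47%. With 20% dropout an arm of 39 falls to 39 × 0.8 ≈ 31. The same formula then gives 8%, 19% and 37% for r = 0.10, 0.20 and 0.30.

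**Effect of adjusting for time since surgery.** In the same simulations with shares of 10% to 30%, a partial correlation given time rejected in about 4% to 6% of runs, with either a linear or a log term. At a 50% share it rejected in about 6% to 8%. The form of the time term matters when early recovery is fast: with a time constant of 15 days, a 30% share and n = 64, a linear term left about 15% and a log term about 6%.

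**The case against.** **The covariate set could be left to an analysis plan.** The article does not say that the correlation will be unadjusted, and an unseen plan may adjust it. That stands as a caution. But the document itself fixes the wide entry window and names a correlation as the analysis for a stated objective, and the weakness comes from that combination.

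**Natural recovery may be part of the target.** The section speaks of postoperative recovery in general, so a correlation that arises because brain and function both evolve after surgery is not obviously wrong. This is a fair reason to keep an unadjusted correlation as a descriptive result. It is not a reason to rely on it alone. Time since surgery precedes both changes, so adjusting for it does not bias a real brain-function link. It asks whether patients at the same stage who change more in ALFF also change more in JOA, at some cost in precision.

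**The premise is plausible but not documented.** No section gives a time course for JOA or ALFF by days since surgery. The Background evidence concerns grey matter volume from before surgery to six months after it, with increases in some regions and decreases in others. It does not concern resting-state ALFF over four weeks. This stands, and it is why no size can be claimed.

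**A single test at 5% is a simplification.** ALFF is computed in every voxel, so the rates above show a mechanism and do not predict the error rate of the imaging analysis. This also stands.

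**A stronger reading.** A reader might infer that the trial will conclude that brain remodelling drives recovery. The document does not say so. Its verbs are exploratory, the design is called exploratory, and the VR mechanism is mentioned as something for which a basis is to be laid.

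**Conclusion.** The point holds in a limited form. As written, the imaging-scale correlation cannot separate a brain-function link from a shared dependence on post-operative stage, and randomization gives no protection inside an arm. This affects a secondary, exploratory analysis only and does not bias the randomized JOA comparison.

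Its size is unknown. The range of roughly 9% to 47% for one arm of 39 (11% to 69% for 64 pooled) rests on assumed variance shares of 10% to 30% in both measures, a uniform spread of entry times, no direct link, and a single Pearson test. If either measure does not depend on time since surgery, the rate stays at 5%. A reader should not infer that the correlation is bound to be spurious, or that a linear adjustment for days always restores the nominal rate; neither is supported.

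**What to change.** In the imaging paragraphs of Statistical analysis, define the association as a partial correlation or regression of ALFF change with JOA change, adjusted for:

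- days from surgery to the baseline scan, in log or another flexible form;
- baseline JOA;
- arm, if the arms are pooled.

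Report any unadjusted correlation as descriptive, and word all results as association only.

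No new data are needed: the surgery date is already required to check inclusion criterion 1, and baseline JOA is measured. The cost is a change of wording and one to a few degrees of freedom. The Trial status section says that recruitment was still under way at submission, so the change could be made before any analysis.
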